#### 4.2.2 Secondary Outcome Measures

Secondary outcomes measures will be measured by:

1. Total number of all-cause ED visits;
2. Total number of all-cause 30-day ED revisits;
3. All-cause 30-day ED revisits rate;
4. Total number of all-cause discharges from IP;
5. Total number of all-cause 30-day IP readmissions;
6. All-cause 30-day IP readmission rate.

Intermediate measures will be measured by:

1. Number and proportion of patients to have identified HRSN;
2. Number and proportion of patients to receive referrals for their HRSN;
3. Number and proportion of patients to receive community-based services to meet their HRSN;
4. Connection to housing resources;
5. Connection to employment resources;
6. Connection to food;
7. Patient-level average of Proportion of Days Covered (PDC) for pharmaceutical prescriptions.

A budget impact analysis will be conducted to estimate the short-term expenditure changes and financial consequences of THRIVE+ compared to THRIVE-Basic, focusing on direct costs of implementation (staffing, resources, eligible intervention population size, etc.).

Post-hoc measures:

1. Social determinants of health services or referrals (e.g., food pantry referrals, food pantry visits, utilities shut-off protection letters).

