Currently, all patients in BMC primary care clinics are eligible to receive the THRIVE-Basic screening at every primary care visit. However, not every patient completes the THRIVE screener at every visit due to staffing shortages, missed opportunities, and patients who decline to be screened. Patients who are screened complete a paper screener, which consists of two parts: part one screens patients for HRSN in the eight domains. Part two asks patients to indicate the resources they want help accessing across the eight domains. Once the patient is in an exam room, a medical assistant enters the screening results into the patients' electronic health record. Patients who request resources in one or more of the domains receive paper guides that describe available hospital and community resources to address the specific domain(s) they indicated. If patients need assistance accessing these resources, they may speak to a clinic-based patient navigator who supports the patients of approximately 12 part-time PCPs and who is also tasked with handling referrals to specialty services. The clinic-based navigator has access to the THRIVE directory to identify resources. The THRIVE directory is a web-based platform and allows for direct communication between community-based organizations and the clinic-based navigator for the purposes of follow-up.

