**THRIVE+ (intervention arm)**

Participants randomized to the intervention study arm will receive the usual care THRIVE-Basic paper screening and Pharmacy Care Program services (just as in the usual care THRIVE-Basic control arm, described above). However, the pharmacy liaison in the THRIVE+ arm will receive additional training to serve as a patient navigator and provide motivational interviewing in order to connect patients with community and hospital resources to address HRSN. Training will include acquisition of patient navigation and motivational interviewing skills through didactics, demonstrations, shadowing, role-plays, reading assignments, and video. The pharmacy liaison-patient navigators will practice the intervention protocol with "practice" participants. Training will also include information about best practices in screening for HRSN (e.g. "normalizing" the process, responding to participants' needs in an empathic and non-judgmental manner). During the intervention, a social worker with experience in motivational interviewing and connecting patients with HRSN to resources will meet every other week with the pharmacy liaison-patient navigators to discuss challenging cases.

The pharmacy liaison-patient navigators will spend the first 30-45 days after participant enrollment in the clinical program helping participants overcome any HRSN identified, above and beyond those brought up by the patient or barriers identified as impacting medication access and adherence. If the participant has not received screening for HRSN within the past three months, the pharmacy liaison-patient navigator will administer the THRIVE screener. For those participants with identified HRSN, the pharmacy liaison-patient navigator will perform a comprehensive assessment and will use the THRIVE directory and other resources to identify resources. The pharmacy liaison-patient navigators may use motivational interviewing skills to address domains in which participants screen positive but do not indicate they want resources. The pharmacy liaison-patient navigators will also provide patient education; assist with appointment-making and reminders; and offer social support, transportation, interpreter and child care services to ensure participants connect with resources to mitigate HRSN.

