The pharmacy liaison-patient navigators will partner with a community organization, Action for Boston Community Development (ABCD). A dedicated ABCD staff member will help connect participants receiving THRIVE+ to ABCD community-based programs, services, and resources at ABCD's decentralized neighborhood sites and centralized departments. Resources include assistance with childcare, employment, utilities, and housing. The pharmacy liaison-patient navigators will initially assess patient needs, formulate recommendations for resources to address HRSN, and interface directly with the dedicated ABCD staff member to coordinate receipt of resources for their patients. Although BMC has a longstanding relationship with ABCD, prior to THRIVE+ there was no designated individual at ABCD to help connect BMC participants to its services, either directly or through their network of affiliations. One 0.5 FTE ABCD employee will be supported to help connect the THRIVE+ participants to services. After the initial 30-45-day intervention period, the pharmacy liaison-patient navigators will contact

participants monthly, re-administering the THRIVE screener every three months to assess for new or unmet HRSN needs until 1 year following enrollment in the clinical program.

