#### **Research Follow-Up Procedures – THIS IS PART 2 OF THE RESEARCH PROVISIONS**

We will assess outcome measures monthly for patients assigned to the THRIVE+ intervention arm, in order to satisfy a requirement of our funder. We will assess all outcome measures for all study participants at 6 months post-enrollment in the clinical program – again, to satisfy a requirement of our funder – and at 12 months post-enrollment in the clinical program.

As part of the research provisions, pharmacy liaisons-patient navigators will systematically screen patients assigned to the intervention arm with the THRIVE screener every three months to assess for new or unmet HRSN. These re-screens will take place during the monthly follow-up touches that are part of the existing clinical program.

We will analyze data collected via routine clinical care to ascertain primary and secondary study outcomes. There are three data sources for data collected as part of routine care:

1. BMC Clinical Data Warehouse
2. BMC HealthNet Claims Data
3. Pharmacy Care Program client tracking system

In addition, we will analyze data collected for research purposes. There is one data source for data collected for research purposes outside of routine clinical care:

1. Connection to resources at Action for Boston Community Development (ABCD), Inc.

To assess receipt of services our community partner for this study, ABCD, will check how many of the intervention arm study participants used services at ABCD to help address HRSN. ABCD will provide BMC with data to confirm patient receipt of services, the type of service received, and the date of receipt.

A Pharmacy Liaison-Patient Navigation Intervention to Reduce Inpatient and Emergency Department Utilization among Primary Care Patients in a Medicaid Accountable Care Organization: A Pragmatic Trial  
Version 1.3, August 5, 2021

611 Table 1. Study Outcomes

| Outcome measure                                                                    | Data Source                                                       | Data collected as part of Routine Care or for Research? | Measurement Time Points (Post-Enrollment)                                                                                                                                              |

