| Patients to receive services to meet their HRSN     | Action for Boston Community Development data                                                                                                       | Research     | Quarterly – All enrolled patients                                                                                                                                                      |
| Connection to housing resources                     | Action for Boston Community Development data                                                                                                       | Research     | Quarterly – All enrolled patients                                                                                                                                                      |
| Connection to employment resources                  | Action for Boston Community Development data                                                                                                       | Research     | Quarterly – All enrolled patients                                                                                                                                                      |
| Connection to food                                  | Action for Boston Community Development data                                                                                                       | Research     | Quarterly – All enrolled patients                                                                                                                                                      |
| Patient-level average of Proportion of Days Covered | BMC HealthNet Plan claims data                                                                                                                     | Routine Care | Quarterly – All enrolled patients                                                                                                                                                      |

|                                        |  |  |  |
|----------------------------------------|--|--|--|
| (PDC) for pharmaceutical prescriptions |  |  |  |
|----------------------------------------|--|--|--|

Table 2. Post-Hoc Measures

| Post-hoc measure                                     | Data Source                 | Data collected as part of Routine Care or for Research? | Measurement Time Points (Post-Enrollment) |

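### Receipt of community-based services is scored only from ABCD, the partner built into THRIVE+, so a between-arm difference could reflect where patients were sent, not whether more of them were served

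*Combined protocol and SAP*

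**What the plan says.** **The outcome.** Protocol 4.2.2 lists as an intermediate measure "Number and proportion of patients to receive community-based services to meet their HRSN", followed by connection to housing, employment and food. Section 12.3 repeats the list. Neither section limits the measure to one organisation.

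**The source.** Protocol Table 1 gives the same single source for all four rows: "Action for Boston Community Development data". The Research Follow-Up Procedures in section 9 confirm that no other source is collected for research: "There is one data source for data collected for research purposes outside of routine clinical care". Of that source the section says "ABCD will provide BMC with data to confirm patient receipt of services, the type of service received, and the date of receipt".

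**ABCD's role.** Section 8 makes ABCD part of the intervention: "A dedicated ABCD staff member will help connect participants receiving THRIVE+ to ABCD community-based programs, services, and resources". A half-time ABCD post is funded for this, and no such contact existed before. THRIVE+ navigators are not confined to ABCD, since they "will use the THRIVE directory and other resources to identify resources".

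**The control route.** Section 8 gives control patients paper guides to hospital and community resources, and the option of seeing a clinic-based navigator. That navigator has the THRIVE directory, which "allows for direct communication between community-based organizations and the clinic-based navigator for the purposes of follow-up".

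**The comparison.** The SAP synopsis, under Statistical method, compares the arms on connection to the community partner and on services received by referral to that partner. It uses logistic regression with odds ratios and 95% confidence intervals. The SAP names no source for these two items. ABCD is the only community partner that the protocol names.

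**The concern.** The outcome's name and its data source do not match. A patient who gets housing or job help from any organisation other than ABCD has no listed route to being counted, in either arm. The omission matters for the comparison because THRIVE+ opens a staffed channel to the one provider that is counted, and usual care does not.

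What is at stake is the mechanism. Protocol 12.1 hypothesises that THRIVE+ raises connection to and receipt of resources and thereby lowers acute utilisation. A difference in ABCD contact could be read as confirming that first step when patients in both arms received help equally often. If utilisation then showed no difference, the trial might be reported as evidence that more services were delivered and did not help. The data could not support that conclusion.

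**Working it through.** **1. Planning figures.** The documents state no receipt rate, no ABCD share and no power for this outcome. The only planning figure used here is the arm size of 182 (protocol 12.2, SAP 3.3). It reproduces if the standard deviation is taken as the square root of the mean, an assumption the documents do not state. The mean is 4.3 + 10.2 = 14.5 visits and a 10% reduction is 1.45. So n = 2 × (1.960 + 1.282)² × 14.5 / 1.45² ≈ 145 per arm, and 145 / 0.80 rounds up to 182. The sample size has no further bearing on this point.

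**2. What is scored.** Let r be the true proportion of patients who receive any community service, and s the share of those recipients served at ABCD. The scored proportion is p = r × s. With equal r, the scored odds ratio is [pT/(1 − pT)] / [pC/(1 − pC)], where T is THRIVE+ and C is control. It equals 1 only if sT = sC.

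**3. Assumptions.** Both arms are looked up. True receipt is equal, at 10%, 20% or 30%. The THRIVE+ share is 50% and the control share runs from 10% to 50%. The test is an uncorrected two-sided chi-square at 0.05 with 182 per arm, standing in for the SAP's logistic regression. The chance of significance is the summed binomial probability of all pairs of counts that reach it.

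**4. One case by hand.** With r = 20%, sT = 50% and sC = 10%, pT = 0.10 and pC = 0.02. The odds ratio is (0.10/0.90) / (0.02/0.98) = 5.4.

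**5. Results.**

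| True receipt, both arms | Control ABCD share | Scored THRIVE+ vs control | Odds ratio | Chance of p < 0.05 |
|---|---|---|---|---|
| 10% | 40% | 5% vs 4% | 1.3 | 7% |
| 10% | 30% | 5% vs 3% | 1.7 | 16% |
| 10% | 10% | 5% vs 1% | 5.2 | 64% |
| 20% | 40% | 10% vs 8% | 1.3 | 10% |
| 20% | 30% | 10% vs 6% | 1.7 | 29% |
| 20% | 10% | 10% vs 2% | 5.4 | 93% |
| 30% | 40% | 15% vs 12% | 1.3 | 14% |
| 30% | 30% | 15% vs 9% | 1.8 | 43% |
| 30% | 10% | 15% vs 3% | 5.7 | 99% |
| any of these | 50% | equal | 1.0 | 5% |

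**6. The direction can also reverse.** Suppose true receipt is lower in THRIVE+, at 30% against 40%, with ABCD shares of 60% and 20%. The scored values are 0.30 × 0.60 = 18% and 0.40 × 0.20 = 8%, which favours THRIVE+.

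**7. Who is looked up.** Section 9 says "ABCD, will check how many of the intervention arm study participants used services at ABCD to help address HRSN". Table 1 gives the same measures quarterly for all enrolled patients, and the SAP compares the arms. These statements conflict. The calculation above takes the reading more favourable to the comparison, and the problem remains under it.

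**The case against.** The strongest reply is that the SAP already uses partner-specific labels, so it claims less than the protocol does. That stands as far as the wording goes. But a partner-specific measure compared between arms is a comparison of exposure to an intervention component, and the protocol's broader outcome remains in 4.2.2, 12.3 and Table 1.

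A second reply is that the SAP has other connection measures for all participants: hospital food pantry referrals and visits, and utility shutoff letters, from the data warehouse. This also stands, and they should be kept. They are hospital-based, however, and do not show receipt from community organisations.

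A third is that the bias is not demonstrated, and this reply is correct. A reader might infer that equal receipt must appear as a THRIVE+ benefit. The documents do not support that. The result needs unequal ABCD shares, which the design encourages but which are nowhere quantified, and a gap of 50% against 40% rarely produces significance. A reader might also infer that control patients score zero by construction because only the intervention arm is checked. One sentence in section 9 points that way, but Table 1 says otherwise. Nor do the documents say that control patients cannot use ABCD.

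**Conclusion.** The concern holds in conditional form. The mismatch between a provider-neutral outcome and a single source tied to THRIVE+ is plain from the protocol, and the SAP plans a between-arm test on partner measures. Equal total receipt could therefore be reported as a THRIVE+ gain.

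How likely that is depends on assumed shares. At 10-30% true receipt and a 50% THRIVE+ share, the chance of a significant result runs from about 7-14% to about 64-99% as the control share falls from 40% to 10%. Other shares would give other figures, so neither end is a bound. The affected measures are intermediate in the protocol and secondary in the SAP's Statistical method row. The composite of admissions and ED visits is untouched, and nothing here bears on its validity.

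**What to change.** - In protocol Table 1 and the SAP's Statistical method row, rename the ABCD-sourced outcomes *use of ABCD services*. Report them descriptively as delivery of THRIVE+, with no between-arm test and no statement about receipt of community-based services.
- Reconcile section 9 (intervention arm) with Table 1 (all enrolled patients) on whom ABCD looks up.
- Keep pantry referrals and visits and utility letters as the between-arm comparison of connection, labelled as hospital-based resources. The protocol lists them as post-hoc (4.2.2, Table 2) and the SAP as secondary (synopsis, 6.1), so the status should be made consistent.
- Name baseline pantry use as an adjustment variable. SAP 4.2 shows the usual care and enhanced arms already differing at inclusion, at 14% vs 25% for referrals and 12% vs 20% for visits.
- Do not substitute THRIVE directory follow-up as a between-arm source. THRIVE+ navigators use it for participants with identified needs, whereas control patients reach it through the clinic-based navigator if they seek help. Nothing says it holds extractable patient-level records of receipt.

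The cost is a change of wording and no new data collection. The trial gives up its between-arm comparison of receipt of community services, a question that the ABCD records cannot answer.

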## 10 Assessment of Safety and Data Safety Monitoring Plan (DSMP)

This study is not greater than minimal risk. For the purposes of this study:

1. An **Unanticipated Problem (UP)** will be defined as an event, experience or outcome that meets all three of the following criteria:
  - a. Is unexpected; and
  - b. Is related or possibly related to participation in the research; and
  - c. Suggests that the research places subjects or others at a greater risk of harm (including physical, psychological, economic, or social harm) than was previously known or recognized.
2. An **Adverse Event (AE)** will be defined as any unanticipated problem or issue regarding confidentiality.

As this study is minimal risk, health-related AEs and Serious Adverse Events (SAEs) are not expected in this minimal risk study and therefore will not be measured.

Unanticipated Problems, Adverse Events, and protocol deviations will be reported to the IRB as required by IRB policies (<http://www.bumc.bu.edu/ohra/hrpp-policies/hrpp-policies-procedures/#6.6.3>).

The study monitor will be the Principal Investigator at Boston Medical Center/BU Medical Campus, and she will report all Adverse Events and Unanticipated Problems to the IRB in compliance with IRB policy, Federal/State regulations, and sponsor requirements (as applicable).

## 11 Data Handling and Record Keeping

### 11.1 Confidentiality

All participants will be assigned a unique study code. We will maintain participant confidentiality in the following ways:

1. The cross-walk that links study codes with identifying information will be kept in a secure network location and in a REDCap database, a database intended for large research studies which can securely manage HIPAA-sensitive data. There will be 2 separate REDCap databases: one solely for identifying information (the mastercode file, including subject name, medical record number, and code) and one solely for study data.
2. Each participant will receive a unique identification number; research data collection and data entry forms will be electronic and identified only with this number. Any hard copy materials will be kept in a locked file in the PI's locked office.
3. Computer systems will be password protected and accessible only to research staff needing the information for follow-up and monitoring purposes.
4. An important issue in web-based data capture is the potential for interception of information posted electronically, and interference with scripts and data stored on the server. To protect against security breaches, data will be electronically encrypted using secure socket layering so that only the intended recipient can decode. All laptops will be secured with password logins so data will be inaccessible in the event a unit is lost or stolen. Files stored on BUMC servers will be protected by electronic 'firewalls' that restrict access to designated users.

## 11.2 Source Documents

Source data/documents needed for this study that are part of the participant's standard of care treatment outside of the research include: (1) THRIVE-Basic screening results; (2) BMC HealthNet Plan claims data; (3) BMC EPIC clinical warehouse data; and (4) Pharmacy Care Program client tracking system.

1. THRIVE-Basic responses will be indicated by participants physically (on paper), and a medical assistant will transcribe the responses (electronically) into the participants' EMR. These data are collected in the routine course of clinical care.
2. We will analyze claims data to evaluate the primary healthcare utilization outcomes (overall hospital admissions; all-cause hospital readmissions; overall ED visits; ED revisits) and for the budget impact analysis.
3. Study outcomes and demographic variables will be obtained from de-identified patient-level data from the BMC clinical data warehouse. These data are collected in the routine course of clinical care.
4. Data will be obtained directly from participants by the clinical staff (the control pharmacy liaisons and the intervention pharmacy liaison-patient navigators). These data are also collected in the routine course of clinical care. Data generated by the methods described in the protocol

(including the Pharmacy Care Program Intake Assessment) will be recorded in the participants' medical records and/or the Pharmacy Care Program client tracking system.

